# The HOSENG trial – Effect of the provision of oral self-testing for absent and refusing individuals during a door-to-door HIV-testing campaign on testing coverage: protocol of a cluster-randomized clinical trial in rural Lesotho

**DOI:** 10.1186/s13063-019-3469-2

**Published:** 2019-08-13

**Keywords:** HIV, Cluster-randomized controlled trial, Village health worker, Community health worker, Community-based, Self-testing, HIV-testing coverage, Lesotho, Southern Africa, Implementation research

## Abstract

**Background:**

HIV-testing coverage remains below the targeted 90% despite efforts and resources invested. Home-based HIV-testing is a key approach endorsed by the World Health Organization (WHO), especially to reach individuals who might not seek testing otherwise. Although acceptance of testing during such campaigns is high, coverage remains low due to absent household members. This cluster-randomized trial aims to assess increase in testing coverage using oral HIV self-testing (HIVST) among individuals who are absent or decline testing during home-based HIV-testing.

**Methods:**

The HOSENG (HOme-based SElf-testiNG) trial is a cluster-randomized, parallel-group, superiority trial in two districts of Lesotho, Southern Africa. Clusters are stratified by district, village size, and village access to the nearest health facility. Cluster eligibility criteria include: village is in catchment area of one of the study facilities, village authority provides consent, and village has a registered, capable, and consenting village health worker (VHW). In intervention clusters, HIV self-tests are provided for eligible household members who are absent or decline HIV-testing in the presence of the campaign team. In control clusters, standard of care for absent and refusing individuals applies, i.e., referral to a health facility. The primary outcome is HIV-testing coverage among individuals aged 12 years or older within 120 days after enrollment. Secondary objectives include HIV-testing coverage among other age groups, and uptake of the different testing modalities. Statistical analyses will be conducted and reported in line with CONSORT guidelines. The HOSENG trial is linked to the VIBRA (Village-Based Refill of ART) trial. Together, they constitute the GET ON (GETting tOwards Ninety) research project.

**Discussion:**

The HOSENG trial tests whether oral HIVST may be an add-on during door-to-door testing campaigns towards achieving optimal testing coverage. The provision of oral self-test kits, followed up by VHWs, requires little additional human resources, finances and logistics. If cost-effective, this approach should inform home-based HIV-testing policies not only in Lesotho, but in similar high-prevalence settings.

**Trial registration:**

ClinicalTrials.gov, (ID: NCT03598686). Registered on 25 July 2018. More information is available at www.getonproject.wordpress.com.

**Electronic supplementary material:**

The online version of this article (10.1186/s13063-019-3469-2) contains supplementary material, which is available to authorized users.

## Background

The United Nations Programme on HIV/AIDS (UNAIDS) has shown a way forward in controlling and finally ending the deadly acquired immune deficiency syndrome (AIDS) epidemic by launching the 90-90-90 strategy [1]. The first target is to ensure that 90% of all people living with human immune deficiency virus (HIV) are aware of their status. The second target is that 90% of those diagnosed receive sustained antiretroviral therapy (ART). And the third target stands for 90% of those receiving ART achieving viral suppression. Globally, in 2017, progress towards the first UNAIDS target, i.e., that 90% of people living with HIV are aware of their status, was lower than other stages of the HIV care cascade [2]. The most recent data from Eastern and Southern Africa show that the percentage of people living with HIV who know their HIV status has steadily improved in the last few years, currently at a level of 81% (64–95%), but still leaving a gap of approximately 1.7 million HIV-positive people to reach the target of 90% knowing their HIV status [3, 4]. In order to reach the first UNAIDS target, home-/community-based testing, i.e., HIV-testing close to where people live or work, is a key strategy endorsed by the World Health Organization (WHO) [5, 6]. Many studies from Southern Africa, including Lesotho, have shown that home-based HIV-testing is highly promising for closing the crucial gap to achieve the first 90 [7]. Yet, it is critical to distinguish between the principal acceptance (uptake) of HIV-testing and the HIV-testing coverage. While in most cases the former is above 90%, the coverage often remains below 90% due to the household members who are absent at the time of the campaign, mainly men and young adults [8].

HIV self-testing (HIVST) has proved to be an accurate diagnostic tool that increases uptake of HIV-testing, facilitates linkage to care among target populations, and may be more cost-effective than provider-delivered HIV-testing [9–17]. Thus, WHO strongly endorses oral HIVST [18]. In a WHO review, 16 countries reported having a policy supportive of HIVST, including Lesotho [19, 20].

However, to date only limited data are available, assessing the effect of oral HIVST in increasing HIV-testing coverage. This randomized controlled trial thus aims to determine the added effect of distributing oral HIVST to individuals absent or refusing to test during a home-based HIV-testing campaign on HIV-testing coverage.

## Methods

### Setting

The HOSENG (HOme-based SElf-testiNG) trial will be conducted in the districts of Butha-Buthe and Mokhotlong, in Northern Lesotho, Southern Africa, in the catchment areas of 22 health facilities. Both districts are characterized by mostly rural settings with an estimated population of 220,000, mainly subsistence farmers and mine workers as well as construction or domestic laborers who work in neighboring South Africa. Each district has only one mid-size town: Butha-Buthe with approximately 25,000 inhabitants, and Mokhotlong with approximately 10,000 inhabitants. The remaining population lives in villages scattered over a mountainous area of 5842 km^2^. According to the recent household-based national survey from 2016 to 2017 the adult HIV prevalence is 17.8% in Butha-Buthe and 26.1% in Mokhotlong [21].

### Design

The HOSENG trial is a cluster-randomized controlled, superiority trial in a resource-limited setting. The rationale for a cluster-randomized design at village level is (1) the reliance of the trial on the village health workers (VHWs) and (2) the high risk of cross-contamination between the study arms if randomization would be done at the individual or household level. The HOSENG trial, with its home-based HIV-testing campaign, provides a recruitment platform for another trial, the VIBRA (Village-Based Refill of ART) trial [22], and thus they are based on the same cluster-randomization and run in parallel. Together, HOSENG and VIBRA [22] constitute the GET ON (GETting tOwards Ninety) research project. To ensure a balance in the exposure to the HOSENG intervention in the two arms, the clusters (villages) will be randomized into four potential groups in a 1:1:1:1 allocation.

### Cluster sampling and randomization

Figure 1 summarizes the cluster sampling and randomization process. A list of all villages with their corresponding VHWs in the study districts was provided by the Ministry of Health and the local District Health Management Teams. Two local members of the research team cross-checked the village list for accuracy. They defined the village size (≥ 30 versus < 30 households) and access to the nearest health facility (easy versus hard to reach, defined by needing to cross a mountain or river or > 10 km away from health facility) by contacting the relevant VHW coordinators. Each village was considered a cluster, except villages which do not have their own VHW and, therefore, form one cluster with neighboring villages served by the same VHW. It is not feasible to visit all clusters (358 villages in Butha-Buthe and 290 villages in Mokhotlong) nor to include more than two VHWs per cluster. Therefore, a random sample of 180 clusters, stratified by district, village size, and access, was taken. If a cluster had more than two VHWs, randomly two VHWs were selected. After excluding clusters who did not meet the eligibility criteria (see next section), the remaining 159 clusters were randomized into the four groups in a 1:1:1:1 allocation ratio with block sizes of 4, stratified by the same stratification factors. All random sampling processes as well as the randomization were performed by an independent statistician. The first 103 clusters will be provided to the research team and will all be enrolled. If needed, further clusters will be released from the randomization list.

**Fig. 1 Fig1:**
[figure not shown]
Cluster sampling and randomization. Abbreviations: *BB* Butha-Buthe, *MKG* Mokhotlong, *VHW* village health worker

### Eligibility criteria

Table 1 outlines the eligibility criteria for clusters and households. No individual eligibility criteria apply for the HOSENG trial as HIV-testing coverage is a population-level outcome including every individual in the surveyed area.

**Table 1 Tab1:** Cluster and household eligibility criteria for the HOme-based SElftestiNG (HOSENG) trial

	Inclusion criteria	Exclusion criteria
Cluster eligibility		
1	The cluster is rural and clearly confined to the catchment area of one of the study clinics a. Note: 1 cluster usually consists of 1 village, but could include several small villages if serviced by the same VHW	The village authority (= village chief) is opposed to trial participation
2	The cluster has at least 1 registered VHW who is willing to participate and fulfills the following criteria: a. is at least 18 years of age b. has adequate reading and writing skills c. successfully passes the training assessment evaluated by a local person independent to the research project and the research team, by checking if the VHW: 1) is able to fill in the assessment (ticking boxes, writing in correct fields) 2) is able to give an adequate answer regarding the open question, which implies adequate reading and writing skills and a basic logical thinking	The VHW is not willing to attend the training or opposed to trial participation or not fulfilling the criteria mentioned in inclusion criteria a. Note: if a cluster entails several VHWs, then the cluster can still participate if there is at least 1 VHW in the cluster who is willing to participate and fulfills the criteria
Household eligibility		
1	Signed informed consent from household head or representative aged 18 years or older	No signed informed consent from household head or representative aged 18 years or older

*VHW* village health worker

Before randomization, all VHWs from the 180 randomly selected villages attend a 1-day refresher training focusing on HIV-testing and counseling (HTC). Every VHW takes a short pre- and post-training assessment. The assessment includes questions about (1) HIV knowledge and HIV stigma using a validated questionnaire [23], (2) HIV-testing knowledge, and (3) one open question (“What are important qualities of a counselor?”). The assessment will be used to evaluate the baseline HIV/AIDS-related knowledge and stigma of the involved VHWs and to evaluate their eligibility for participation in the trial (Table 1).

Prior to trial start, the research team met with all relevant village chief councils in order to inform them about the trial and to obtain their consent.

### Procedure

Two to three specifically trained teams, each consisting of five to six lay-counselors, one campaign organizer and one supervising study nurse will visit all households in selected villages, going from door to door. The teams will propose HTC and multi-disease screenings and prevention. The population of the selected areas are informed about the campaign beforehand by their village chief. Specifically, the campaign team will arrive in the village in the morning, meet with the village chief and then start systematically visiting all households in the pre-defined area by going from door to door. At the household, the teams will proceed as follows:The counselor will introduce him- or herself and explain the purpose of the testing/screening campaignThe counselor will ask the head of household or their representative (aged 18 years and older) for written informed consent to the testing/screening campaign, and to obtaining data about present and absent household members for study purposeIf the head of household or the representative refuses their household participation, the team will leave the house, record the refusal reason, and proceed to the next householdThe counselor will assess the total number of present and absent household membersDefinition of household member: (1) is acknowledged by the household head or the representative as part of the household and (2) sleeps in the household regularly (at least once a month), and (3) if absent during the campaign: returns to the household no later than 3 months after the date of the home visitThe counselor will provide information about HIV and testing, prevention aspects, and the other disease screenings (see below)The counselor will assess the HIV status of all household members and screen the patient’s health booklets (“*bukana*”)Household members who are eligible for and consent to testing (by filling in the Lesotho national informed consent form for HIV-testing) undergo HIV-testing by the counselor according to specific cluster-arm allocation procedure and according to national HIV-testing guidelines [20]. For absent or declining household members the specific procedures differ between the two cluster arms and are described in detail below in the section on intervention clusters. Figure 2 presents all possible HIV-testing scenarios during the campaignOnce the HIV test is done, the counselor documents the result in the patient’s health booklet and provides post-test counseling. If the HIV test is confirmed positive, the counselor contacts the study nurse, who then provides further counseling and assesses the participant for enrollment into the inter-linked follow-up study (VIBRA trial [22])

**Fig. 2 Fig2:**
[figure not shown]
HIV-testing scenarios in HOme-based SElftestiNG (HOSENG) trial. Scenarios 2 and 3 only occur in the HOSENG intervention clusters

The HIV-testing campaign is combined with additional multi-disease screening. The campaign screens for tuberculosis (TB) according to national guidelines using the clinical symptom screening tool [24]. If TB is suspected, one sputum sample is collected on the spot, transported to the health facility the same day by the campaign team for testing with GeneXpert. Another sputum bottle for collecting a morning sample is left behind, the individual is instructed on how to use it and a follow-up plan for collection (i.e., collection by VHW) is agreed upon. Further campaign services include alcohol abuse screening using the CAGE questionnaire [25], information and referral of men aged 15–50 years (HIV-negative and -positive due to stigma reasons) for voluntary medical male circumcision (VMMC) according to WHO recommendations [26], and promotion and provision of male condoms. Figure 3 presents the overview of the HIV and multi-disease campaign and its algorithm.

**Fig. 3 Fig3:**
[figure not shown]
Algorithm of the human immune deficiency virus (HIV) and multi-disease screening/prevention campaign

#### Intervention clusters

Figure 4 summarizes the procedures in the HOSENG clusters and Fig. 5 the Standard Protocol Items: Recommendations for Interventional Trials (SPIRIT) flow diagram. In the intervention clusters, the campaign team will leave an oral HIVST kit (OraQuick® ADVANCE HIV I/II, second generation serology assay with a sensitivity of > 93%, a specificity of > 99 [27–30]) for every household member aged 12 years or older who is absent or declined HIV-testing on the day of the campaign. We chose 12 years as the threshold because adolescents are an important risk group and this is the legal age for providing HIV-testing consent in Lesotho [24]. The household can refuse to have an oral HIVST left behind for their absent household members. The oral HIVST kit is prepacked, includes a written and pictoral instruction for use in the local language, Sesotho, and the package is labelled with a written request to consult the VHW within 2 weeks after use of the test – irrespective of the result. In cases where more than one trained VHW serves the village, the household will be asked for the VHW of choice. The team will label the kit with the name of the absent member before dispensation.

**Fig. 4 Fig4:**
[figure not shown]
Description of the procedure in the HOme-based SElftestiNG (HOSENG) intervention and control clusters. Mobilizing: through village chief before the campaign date, and through the campaign team on the day of the campaign by going from door to door. Further services include: screening for tuberculosis, screening for alcohol abuse, voluntary medical male circumcision and condom provision

**Fig. 5 Fig5:**
[figure not shown]
Standard Protocol Items; Recommendations for Interventional Trials (SPIRIT) flow diagram of the HOme-based SElftestiNG (HOSENG) trial

One household member – the one with the closest relation to the absent person(s) – will be tested and trained using the oral HIVST. All other present household members will be tested using the standard blood-based point-of-care HIV test according to Lesotho national guidelines [20].

The VHWs in the intervention custers will receive a list of all household members for whom an oral HIVST was dispensed. The VHW will visit all households 2–4 weeks after the campaign to collect the oral HIVST in case the oral HIVST is not returned to the VHW. If an oral HIVST is reactive, the VHW will either provide further blood-based testing on the spot or organize referral to the nearby health facility for confirmatory testing. All VHWs from intervention clusters will receive a second extensive training session about oral HIVST, handling disclosure and stigma, and data entering on paper-based study forms and the patient’s health booklet.

#### Control clusters

Following standard of care during home-based HIV-testing, every absent household member or those declining HIV-testing will be encouraged to get an HIV test done by the VHW or the nearby health facility. The research team will screen the registers at the health facilities in order to assess if these individuals came for testing in the timeframe of the primary endpoint window.

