### Sample size

The sample size is driven by the VIBRA trial [22]. We assume that to achieve the VIBRA trial [22] sample size (minimum 262 HIV-positive individuals not on ART) by testing about 10,000 individuals in 100 villages, based on a previous trial [32]. According to a previous home-based HIV-testing campaign [33], we estimate an HIV-testing coverage rate of individuals aged 12 years or older in rural villages of 63%. We consider a 15% increase in coverage as relevant from a policy perspective. Using an intra-cluster correlation (ICC) of 0.028, with a sample of 100 clusters, we will require a sample size of 450 in order to have > 90% power to detect an increase in coverage rates to 78% or higher. This corresponds to an increase of 1.17 (variance inflation factor (VIF)) from the 386 individuals required in the absence of clustering. If we vary the ICC for villages and include an additional ICC for clustering at the household level [34], the maximum VIF would be 8.3 corresponding to a maximum sample size of 3204 needed to ensure 90% power to detect a 15% difference, well below the expected 10,000 individuals to be included. Table 3 displays the sample size calculations considering all relevant factors under different scenarios.

**Table 3 Tab3:** Sample size estimations for the HOme-based SElftestiNG (HOSENG) trial

Average village size	Average household size	ICC (village)	ICC (household)	VIF	Total number of clusters	Total sample size
30	2	0.028	0.05	1.04	100	402
30	2	0.028	0.1	1.07	100	413
30	2	0.05	0.05	1.20	100	462
30	2	0.05	0.1	1.34	100	518
30	2	0.1	0.05	2.95	100	1139
30	2	0.1	0.1	4.4	100	1699
30	4	0.028	0.01	1.06	100	410
30	4	0.028	0.05	1.31	100	507
30	4	0.028	0.1	1.62	100	628
30	4	0.028	0.5	4.12	100	1592
30	4	0.05	0.01	1.09	100	420
30	4	0.05	0.05	1.44	100	556
30	4	0.05	0.1	1.88	100	726
30	4	0.05	0.5	5.4	100	2085
30	4	0.1	0.01	1.15	100	442
30	4	0.1	0.05	1.73	100	668
30	4	0.1	0.1	2.46	100	950
30	4	0.1	0.5	8.3	100	3204

*ICC* intracluster correlation coefficient, *VIF* variance inflation factor

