Baseline characteristics will be presented according to randomized groups; no formal testing will be performed. Categorical variables will be described with absolute and relative frequencies and continuous variables with medians and interquartile ranges. As with the primary analysis, secondary endpoints will be analyzed with multi-level logistic regression models including village and household as random effects. All results will be presented as odds ratios and 95% confidence intervals. The potential effect modification of sociodemographic determinants (age groups, gender, education status, employment status, HIV-testing history) on all endpoints will be assessed by including interaction terms in the models. If the Wald test results for the interaction terms are significant, intervention effects will be presented separately by the levels of these factors. Sensitivity analyses will be conducted in order to provide evidence that the result seen from the primary analysis are robust. In order to assess the reliability of the model fit, we will perform a quadrature check. In case of unreliable model fit, we will use generalized estimating equations to fit our model which will provide population-averaged odds ratios and 95% confidence intervals. However, this model would not allow inclusion of more than one random effect although including the highest level of clustering is suggested to be sufficient [38]. All analyses will be done using Stata (version 14, Stata Corporation, Austin, TX, USA). For all tests, we will use two-sided *p* values with an alpha = 0.05 level of significance.

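### For household members absent or declining on campaign day, the follow-up sources for the 120-day primary endpoint are described differently in the two arms

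*Protocol article*

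**What the plan says.** Under Control clusters, the protocol article names two places for a later test: "every absent household member or those declining HIV-testing will be encouraged to get an HIV test done by the VHW or the nearby health facility". That section's next sentence names one source for finding it: "The research team will screen the registers at the health facilities in order to assess if these individuals came for testing". The abstract (Methods) describes the control condition more narrowly: "standard of care for absent and refusing individuals applies, i.e., referral to a health facility".

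Under Intervention clusters, the VHW receives a list of the members for whom a kit was dispensed and follows those kits up: "The VHW will visit all households 2–4 weeks after the campaign to collect the oral HIVST in case the oral HIVST is not returned". Intervention VHWs also get a second training that covers data entry on study forms and in the health booklet. Data collection and management describes VHW study forms only for dispensed kits. No register search is described for this arm.

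VHWs from all sampled villages had basic preparation before randomization; under Eligibility criteria they "attend a 1-day refresher training focusing on HIV-testing and counseling (HTC").

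The Endpoints section defines a confirmed result in the same words for both arms and puts every resident aged 12 or older in the denominator. It does not set a common procedure for finding results after the home visit. Under Procedure, household enumeration, campaign-day testing of those present and booklet screening happen in both arms.

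**The concern.** Coverage is a proportion of all enumerated residents, so a test that took place but was not found is counted in the same way as no test. If the chance of finding a test depends on arm, the primary comparison mixes the effect of the kits with a difference in recording. It does so among absent and declining members, who are the people the intervention is meant to reach.

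There are two gaps, and they pull in opposite directions. A control member who follows the advice and tests with the VHW has no described route into the data, which would make the intervention look better than it is. An intervention member who goes to a facility, or whose household refused the kit and who tests there later, has no described route either, which would make it look worse. The planned incremental cost per additional confirmed result would carry the same error.

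**Working it through.** **1. Follow-up sources as written, for members without a result on campaign day**

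| Source | Control | Intervention |
|---|---|---|
| Health booklet at the home visit | yes | yes |
| Facility registers within the window | yes | not described |
| VHW study forms | not described | yes, for dispensed kits |
| VHW home visit | not described | yes, to collect kits not returned |
| VHW training in study forms and booklet entry | not described | yes |

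The kit and the VHW contact about it belong to the intervention. The register search and the recording of conventional tests are measurement, and could be identical in both arms.

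**2. The plan's own figures**

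Inputs from Sample size and Analyses: control coverage ("we estimate an HIV-testing coverage rate of individuals aged 12 years or older in rural villages of 63" percent), target and power ("> 90% power to detect an increase in coverage rates to 78% or higher"), and two-sided "values with an alpha = 0.05 level of significance".

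Per arm, with pooled variance and mean proportion 0.705:

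n = [1.96 × √(2 × 0.705 × 0.295) + 1.2816 × √(0.63 × 0.37 + 0.78 × 0.22)]² / 0.15² = (1.264 + 0.815)² / 0.0225 ≈ 192.2, rounded up to 193.

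The total is 386, as stated. 386 × 1.17 = 451.6, against the stated 450. The planning figures are therefore understood correctly. They do not bear on whether ascertainment is equal.

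**3. Size of a recording gap**

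Let f be the share of people recorded as not covered who do have a result. The documents give no value for f; 5–20% is assumed. Understatement = f × (1 − recorded coverage).

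| f | Control: f × 0.37 | Intervention: f × 0.22 |
|---|---|---|
| 5% | 1.9 points | 1.1 points |
| 10% | 3.7 points | 2.2 points |
| 20% | 7.4 points | 4.4 points |

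The intervention base is 22% because planned coverage there is 78%.

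Recorded difference minus true difference = control understatement − intervention understatement. With f between 5% and 20% in each arm, this runs from 1.85 − 4.4 = −2.55 points to 7.4 − 1.1 = +6.3 points. If only one arm is affected, the extremes are −4.4 and +7.4.

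On the odds-ratio scale, a recorded 78% v 63% gives (0.78/0.22)/(0.63/0.37) = 2.08. If 10% is missed in control only, true control coverage is 66.7% and the true odds ratio is (0.78/0.22)/(0.667/0.333) = 1.77. If 10% is missed in intervention only, true intervention coverage is 80.2% and it is (0.802/0.198)/(0.63/0.37) = 2.38.

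**4. Does the large sample protect?**

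Take about 10,000 people in 100 villages, 5,000 per arm, true coverage of 63% in both arms, and control recorded 3.7 points lower with no offsetting gap in intervention. The variance inflation factor is 1 + 99 × 0.028 = 3.77 at 100 people per village, or 8.3 at the plan's maximum. The effective number per arm is 5,000/3.77 ≈ 1,326 or 5,000/8.3 ≈ 602. The chance of a significant result favouring the intervention is then about 50% or 26%, against a nominal 2.5%. This is a one-direction illustration, not a forecast.

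**The case against.** The strongest reply is that this is a condensed article and that much here is silence. That is partly right, and it limits what can be said.

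- A reader might infer that control VHW tests are never counted. No passage says so. Such tests might reach facility registers or booklets, and Figures 2 and 4, which show the testing scenarios and the procedures by arm, could not be read for this point. What stands is that no route for counting them is described.
- A reader might infer that the whole endpoint comes from different sources by arm. It does not: campaign-day tests and booklet checks are shared. Only follow-up of absent and declining members differs.
- A reader might infer that intervention VHWs record results for every household. Their list and forms cover dispensed kits, and the visit is to collect kits not returned.
- A reader might infer that absent control members on ART are systematically missed because the register sentence speaks of coming for testing. That is speculative: status is assessed for all household members at the visit, and proof of ART is not stated to be limited to booklets.
- Kit return and VHW contact are part of what is being tested, so higher recorded coverage through them is not simply an artefact.
- The shares in the illustration are assumed, and the protocol does not say whether 63% includes testing after the campaign.

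The point survives because the article is not merely brief here. It sets out follow-up arm by arm, and what it sets out is unequal. It recommends two test sites in control and names a source for one of them. Booklet screening belongs to the campaign visit, and no later booklet review in control is described.

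**Conclusion.** The concern holds for absent and declining members aged 12 or older. Followed as written, the protocol would find their later tests through different sources in each arm. The net direction and size of any bias cannot be derived from the documents, so a claim that the result must favour the intervention is not supported. Under the assumed 5–20%, the recorded difference could be off by a few points either way, which is not small beside a 15-point target. A large sample does not remove such an error. The abstract and the body also differ on where control members are sent; this is a minor inconsistency, but it concerns the very route that lacks a source.

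**What to change.** 1. At day 120, search the same facility registers, by the same rule, for every listed member aged 12 or older without a confirmed result, in both arms.
2. Collect VHW testing records in control clusters and count those tests by the rule used in intervention clusters.
3. Add a sensitivity analysis that keeps self-test results but drops conventional tests found through a source searched in one arm only. Restricting it to sources present in both arms would be wrong, because it could discard the self-tests that are the intervention effect.
4. Reconcile the abstract's account of control referral with the Control clusters section.

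The cost is a longer name list for a register search already planned, plus a small effort to collect and enter control VHW records.

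Timing matters. With launch on 26 July 2018, a recruitment period of up to 8 months and a 120-day window, planned follow-up ends around 24 July 2019, before publication of the article on 13 August 2019. If that schedule was kept, the register search can still be done retrospectively where registers are kept, but VHW tests that were never logged cannot be recovered. In that case the report should state which sources were used in each arm and give the number of results from each.
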